#### Imaging

We will assess the articular cartilage in the lateral compartment of the knee, using quantitative *magnetic resonance imaging* (qMRI). Specifically, T1rho and T2 relaxation times are sensitive to changes in collagen and proteoglycan content of articular cartilage [42, 43], typically observed following ACL injury [44, 45]. Increases in T1rho or T2 relaxation time have been shown to be predictive of the development of OA [46]. Participants will undergo MRI at 24 months postoperative. Participants with a meniscal root tear will undergo MRI at 12 months and 24 months postoperative to assess healing. Scans will be performed on a 3 T Siemens Magnetom Trio magnet, and a 15-channel Siemens PRISMA knee coil (Siemens Medical Solutions, New Jersey, USA). qMRI pulse sequences consist of a Sagittal Multi-Echo Spin Echo T2 Mapping sequence, and a 16-shot Gradient Echo T1rho Mapping sequence.

We will also evaluate radiographical evidence of OA using plain anteroposterior, Rosenberg and lateral view radiographs. Joint space degeneration will be evaluated by a clinician using the Kellgren-Lawrence Grading Scale [47], which ranges from 0 (normal joint space) to grade 4 (large osteophytes, marked narrowing of joint space, severe sclerosis and deformity of bone contour).

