### Plan for statistical analysis

We will determine the absolute risk of graft failure in each group, calculate a relative risk (RR) and risk difference (RD) of graft failure with 95% confidence intervals around the estimate and use a Mantel Haentzel Test (random effect of surgeon) to determine the significance of the association between the addition of LET and graft failure rates. We will calculate the number needed to treat (NNT) to describe the number of patients who need to receive LET to prevent one graft failure over the first two postoperative years. We will calculate the mean and standard error (ACL-QOL, KOOS, EuroQoL) for each group at each time point and calculate the mean between-group difference with 95% confidence interval at 1 and 2 years postoperative. We will perform mixed model analyses, where time is a categorical fixed effect; treatment group, and sex are fixed effects, and patient and surgeon are random effects, to determine whether the difference between groups is of sufficient magnitude to make a definitive conclusion about the effectiveness of ACLR with LET compared to ACLR alone. Then, we will plot each health status score by time and by group to illustrate the change over time. We will conduct a similar analysis for all continuous outcome variables. Finally, for ease of interpretability, we will calculate the number of patients in each group who achieve a change at least as large as the MCID for an individual patient. We will present the NNT to describe the number of patients who need to undergo LET for one person to achieve an important change in HRQOL.

For qMRI analysis, T1rho and T2 relaxation maps are generated using software developed in-house by fitting image intensities of the T1rho and T2 weighted images pixel-by-pixel to the eq. S(TE) ∝ exp.(−TE/T2) using a Levenberg-Marquardt mono-exponential fitting algorithm. Load-bearing central, anterior, and posterior regions of medial and lateral articular cartilage of the femur and tibia are manually segmented and analyzed using 3D Slicer software. The reader is blind to scan order. We will use an independent t-test to evaluate whether the T1rho and T2 relaxation times between groups for all nine cartilage segments are statistically significant. We will present means, standard deviations and 95% confidence intervals for interpretation.

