## Data collection methods

The timing of follow-up assessments corresponds with regular visits to the surgeon following ACLR. During these visits, the research assistant will administer the questionnaires to ensure they are complete. Alternatively, the patient can complete the questionnaires online within the visit window by directly accessing the electronic data capture (EDC) system (*Empower Health Research*). A blinded surgeon will complete the knee exam and a blinded kinesiologist will conduct the hop and strength tests within the clinic at 6, 12, and 24 months postoperative. Participants will complete the DVJ test at their 6- and 12-month visit in WOBL. MRI’s will be conducted at Robarts Research Institute located adjacent to the lead site and a radiologist, blind to group allocation, will report MRI findings using a standardized form.

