## Discussion

ACL injury is one of the most common orthopedic knee injuries and, despite advances in surgical technique and rehabilitation protocols, up to 30% of patients will re-tear their graft or suffer a contra-lateral ACL injury with younger age groups particularly at risk [16, 49]. Persistent instability leads to worse patient outcomes following ACLR and biomechanical cadaveric studies have shown that an ACLR alone may be insufficient to restore normal rotation. A 2015 meta-analysis of 29 studies (8 randomized, 21 non-randomized) comparing ACLR alone with ACLR and LET found the addition of a LET reduces rotational laxity by a statistically significant amount however, studies comparing the two procedures demonstrated limitations including small sample size and potential risk of bias [31].

The protocol for the *Stability Study* is the first adequately powered RCT to study the effects of whether augmenting ACLR with a LET reduces failure in young, high-risk patients. Two further potential strengths of this study are the addition of functional and biomechanical testing and quantitative MRI to the protocol. Functional and biomechanical testing are measures of neuromuscular training and patterning that require muscle strength, proprioception and balance to complete [50], all of which are important components in rehabilitation and injury prevention [51, 52]. Despite high re-injury rates and issues returning to pre-injury levels of sport following ACLR, few high-quality studies include comparison of functional and biomechanical outcomes between groups [53].

Concerns that the addition of an LET to the lateral side of the joint may increase the risk of post-traumatic OA will be addressed by the addition of qMRI to the trial. A recent systematic review found that radiographic evidence of OA was not significantly increased in patients where ACLR was augmented with LET compared to ACL alone [54]. Patients were assessed for radiographic evidence of OA however follow-up length and results were variable between studies. Using qMRI to evaluate cartilage degeneration allows us to compare articular cartilage health between groups through T1Rho and T2 relaxation times; increased relaxation times have been shown to be predictive of the development of OA [46].

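### The osteoarthritis concern about LET is assigned to qMRI, but the fixed analysis is a set of unadjusted t-tests judged by significance, which can detect harm but cannot exclude it

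*Protocol article*

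**What the plan says.** In the Discussion of the protocol article, concerns that an LET on the lateral side of the joint "may increase the risk of post-traumatic OA will be addressed by the addition of qMRI to the trial". The same paragraph says that longer relaxation times predict OA, so harm has a known direction.

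The Plan for statistical analysis gives the method: "We will use an independent t-test to evaluate whether the T1rho and T2 relaxation times between groups" "for all nine cartilage segments are statistically significant". It continues: "We will present means, standard deviations and 95% confidence intervals for interpretation". The segments cover medial and lateral cartilage, although the Imaging section describes the qMRI aim as assessing the lateral compartment.

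On who is scanned, the Imaging section says "Participants will undergo MRI at 24 months postoperative", and Table 2 lists the two-year MRI without restriction. Under Data collection methods, however, the MRIs "will be conducted at Robarts Research Institute located adjacent to the lead site", while Study setting lists seven Canadian and two European sites. No MRI sample size is given.

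The Allocation section stratifies randomisation by surgeon, sex and meniscal repair status. For the patient-reported scores, the analysis plan specifies mixed models with sex as a fixed effect and surgeon as a random effect, and extends a similar analysis to every continuous outcome.

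OA is also assessed by another route: "We will also evaluate radiographical evidence of OA using plain anteroposterior, Rosenberg and lateral view radiographs", graded by Kellgren-Lawrence. Radiographic OA is recorded as an adverse event as well.

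**The concern.** The question is whether LET makes cartilage worse. The stated criterion is whether a difference in either direction reaches significance. A test of equality can show harm when it rejects. When it does not reject, it says nothing about how much harm remains possible, and only the confidence interval does. The article promises intervals but does not say that they, rather than the p-values, will carry the OA conclusion. If few patients are scanned, non-significance is the likely result even under a real increase, and a reader could take it as reassurance about cartilage.

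Two features of the fixed method make the answer less sharp. All 18 tests have equal standing, although the concern is lateral. The comparison also omits the factors used to stratify randomisation, without a stated reason for departing from the article's own adjusted model for continuous outcomes.

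**Working it through.** **The plan's own figure.** The only power statement concerns the primary outcome. With control risk p1 = 0.25 (lower end of the stated range), a 40% relative reduction (p2 = 0.15), mean risk p = 0.20, two-sided 5% and 80% power:

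n = [1.96·√(2·p·(1−p)) + 0.842·√(p1(1−p1) + p2(1−p2))]² / (p1−p2)² = [1.96·√0.32 + 0.842·√0.315]² / 0.10² = 250 per group.

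The article states 255, which gives 80.8% power, and 255/(1 − 0.15) = 300 per group. So 255 per arm is the number expected to be evaluable if every participant were scanned. There is no corresponding figure for qMRI.

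**Power and precision of one qMRI t-test.** Assumptions, because the article gives none: true increase of 0.3 SD in one segment, two-sided 5%, equal arms. The non-centrality parameter is 0.3·√(n/2) with 2n − 2 degrees of freedom. The 95% half-width in SD units is t(0.975)·√(2/n).

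| n per arm | Non-centrality | Power at 0.3 SD | Chance of non-significance | 95% half-width (SD) |
|---|---|---|---|---|
| 50 | 1.50 | 32% | 68% | 0.40 |
| 100 | 2.12 | 56% | 44% | 0.28 |
| 255 | 3.39 | 92% | 8% | 0.17 |

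With 50 per arm and an observed difference of exactly zero, the interval still reaches an increase of 0.40 SD. With 255 it reaches 0.17 SD.

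**Numbers needed to exclude an increase.** With a true difference of zero, one-sided 2.5% (the upper limit of a two-sided 95% interval) and 80% power, n per arm = 2·(1.96 + 0.842)²/M² for a margin of M SD. This gives 63 for M = 0.5, 175 for M = 0.3 and 393 for M = 0.2. These margins are illustrations, not proposals.

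**Number of tests.** Nine segments × two measures = 18. If all nulls were true and the tests independent, the chance of at least one significant result would be 1 − 0.95^18 = 60%. The measures are surely correlated, so this is only a guide to scale. It is an error towards declaring a difference.

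**Cost of omitting the stratification factors.** If they explain a share R² of the variance in relaxation time, the unadjusted interval is wider by about 1/√(1 − R²): 1/√0.90 = 1.05 at R² = 0.10 and 1/√0.80 = 1.12 at R² = 0.20. The R² values are assumptions, since the article gives no basis for them.

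**The case against.** The strongest reply is that the article contains no rule turning non-significance into a safety claim. It commits to 95% confidence intervals for interpretation, and the upper limit of such an interval is what a careful reader needs. That stands. A reader might infer that a null result will be reported as safety, but no sentence says so. The point is only that the wording leaves the misreading open.

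A reader might also infer that the MRI sample is small. The Imaging section and Table 2 schedule the scan without restriction. A single MRI facility in a nine-site international trial makes a subset likely, but its size is unknown, and with about 255 per arm most of the problem disappears.

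Nor does the t-test carry the OA question alone, because radiographs and adverse-event recording also bear on it. And the lack of a harm margin is not in itself a fault of a journal article, since one may stand in the full protocol or analysis plan.

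An unadjusted t-test in a randomised comparison is valid. The loss is in precision, and its size is assumed. The qMRI paragraph could also be read as a deliberate exception to the general rule for continuous outcomes, though no reason is offered.

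Finally, the miss rates above apply to one test. If LET affected several segments or both measures, the chance that all 18 tests would be non-significant is lower.

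What remains is the mismatch between a question about harm and a significance criterion, together with a stated method that has a better replacement at almost no cost.

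**Conclusion.** The point holds in limited form. The article assigns a one-directional harm concern to qMRI and fixes unadjusted significance tests that cannot by themselves exclude that harm. How much this matters depends on a number the article does not give. At 50 per arm, a 0.3 SD increase in a segment would be missed in about two of three trials (serious). At 255 per arm it would be missed in about one of twelve (minor). These figures rest on an assumed effect in SD units and on single-segment tests. The loss of precision from omitting the stratification factors is about 5% to 12% of interval width under an assumed R² of 10% to 20%.

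The documents do not support saying that the investigators will treat non-significance as proof of safety, that the MRI sample is known to be small, or that OA is judged by this test alone.

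**What to change.** Replace the t-test with a linear model for the LET minus ACLR difference in relaxation time, adjusted for sex and meniscal repair, with surgeon as a random effect. This respects the stratification and brings qMRI into line with the approach already planned for other continuous outcomes.

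Before unblinding:

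- Name one lateral-compartment contrast as the lead and treat the other segments and the second measure as supporting.
- State that the OA conclusion rests on the upper 95% limit of the adjusted difference, judged against a threshold if one can be agreed.
- State that a result which neither shows an increase nor excludes a relevant one will be reported as inconclusive, and that non-significance will not be described as absence of harm.
- State which participants receive the 24-month MRI and how many are expected.

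Radiographic OA remains supporting evidence. The cost is a change of analysis wording and, if feasible, one agreed threshold, with no new data. The downside is that the conclusion on cartilage safety may have to be reported as inconclusive.

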## Data collection methods

The timing of follow-up assessments corresponds with regular visits to the surgeon following ACLR. During these visits, the research assistant will administer the questionnaires to ensure they are complete. Alternatively, the patient can complete the questionnaires online within the visit window by directly accessing the electronic data capture (EDC) system (*Empower Health Research*). A blinded surgeon will complete the knee exam and a blinded kinesiologist will conduct the hop and strength tests within the clinic at 6, 12, and 24 months postoperative. Participants will complete the DVJ test at their 6- and 12-month visit in WOBL. MRI’s will be conducted at Robarts Research Institute located adjacent to the lead site and a radiologist, blind to group allocation, will report MRI findings using a standardized form.

## Discussion

ACL injury is one of the most common orthopedic knee injuries and, despite advances in surgical technique and rehabilitation protocols, up to 30% of patients will re-tear their graft or suffer a contra-lateral ACL injury with younger age groups particularly at risk [16, 49]. Persistent instability leads to worse patient outcomes following ACLR and biomechanical cadaveric studies have shown that an ACLR alone may be insufficient to restore normal rotation. A 2015 meta-analysis of 29 studies (8 randomized, 21 non-randomized) comparing ACLR alone with ACLR and LET found the addition of a LET reduces rotational laxity by a statistically significant amount however, studies comparing the two procedures demonstrated limitations including small sample size and potential risk of bias [31].

The protocol for the *Stability Study* is the first adequately powered RCT to study the effects of whether augmenting ACLR with a LET reduces failure in young, high-risk patients. Two further potential strengths of this study are the addition of functional and biomechanical testing and quantitative MRI to the protocol. Functional and biomechanical testing are measures of neuromuscular training and patterning that require muscle strength, proprioception and balance to complete [50], all of which are important components in rehabilitation and injury prevention [51, 52]. Despite high re-injury rates and issues returning to pre-injury levels of sport following ACLR, few high-quality studies include comparison of functional and biomechanical outcomes between groups [53].

Concerns that the addition of an LET to the lateral side of the joint may increase the risk of post-traumatic OA will be addressed by the addition of qMRI to the trial. A recent systematic review found that radiographic evidence of OA was not significantly increased in patients where ACLR was augmented with LET compared to ACL alone [54]. Patients were assessed for radiographic evidence of OA however follow-up length and results were variable between studies. Using qMRI to evaluate cartilage degeneration allows us to compare articular cartilage health between groups through T1Rho and T2 relaxation times; increased relaxation times have been shown to be predictive of the development of OA [46].

High graft failure rates following ACLR, particularly in young, active patients, are concerning and need to be addressed. It has been suggested that poor rotational control following ACLR may predispose patients to graft failure, which leads us to believe there may be a role for augmenting the ACLR with an extra-articular reconstruction. Previous studies combining ACLR and a LET showed promising results, though small sample sizes and potential biases limit the conclusions we can make. The Stability study protocol is for a multicenter, international, adequately powered RCT comparing ACLR alone to ACLR combined with an LET. This study can provide level-one evidence regarding the effect augmenting an ACLR with a LET has on graft stability, patient quality of life, functional performance, biomechanics, and radiographic outcomes, and has the potential to change clinical practice.

## Abbreviations

ACL: Anterior cruciate ligament
ACLQOL: Anterior Cruciate Ligament Quality of Life Questionnaire
ACLR: Anterior cruciate ligament reconstruction
AE: Adverse event
AR: Absolute risk
DVJ: Drop Vertical Jump
EDC: Electronic data capture
Euro-Qol: European Quality of Life Scale
HRQOL: Health-related quality of life
IKDC: International Knee Documentation Committee Subjective Knee Form
KOOS: Knee Osteoarthritis and Outcome Scores
LEFS: Lower Extremity Functional Score
LET: Lateral extra-articular tenodesis
MARS: Marx Activity Rating Scale
MRI: Magnetic resonance imaging
NNT: Number needed to treat
OA: Osteoarthritis
P4: Four-Item Pain Intensity Measure
QALY: Quality-adjusted life years
qMRI: Quantitative magnetic resonance imaging
RCT: Randomized clinical trial
RD: Risk difference
ROM: Range of motion
RR: Relative risk
RRR: Relative risk reduction
VAS: Visual analog scale
WOBL: Wolf Orthopaedic Biomechanics Laboratory
